## Abstract

**Background:**

Natural orifice specimen extraction surgery for colorectal cancer has been introduced in order to reduce the abdominal incision, demonstrating major development potential in minimally invasive surgery. We are conducting this randomized controlled trial to assess whether robotic NOSES is non-inferior to traditional robotic-assisted surgery for patients with colorectal cancer in terms of primary and secondary outcomes.

**Method/design:**

Accordingly, a prospective, open-label, randomized controlled, parallel-group, multicenter, and non-inferiority trial will be conducted to discuss the safety and efficacy of robotic natural orifice extraction surgery compared to traditional robotic-assisted surgery. Here, 550 estimated participants will be enrolled to have 80% power to detect differences with a one-sided significance level of 0.025 in consideration of the non-inferiority margin of 10%. The primary outcome is the incidence of surgical complications, which will be classified using the Clavien-Dindo system.

**Discussion:**

This trial is expected to reveal whether robotic NOSES is non-inferior to traditional robotic-assisted surgery, which is of great significance in regard to the development of robotic NOSES for patients with colorectal cancer in the minimally invasive era. Furthermore, robotic NOSES is expected to exhibit superiority to traditional robotic-assisted surgery in terms of both primary and secondary outcomes.

**Trial registration:**

ClinicalTrials.govNCT04230772. Registered on January 15, 2020.

## Introduction

Laparoscopic natural orifice specimen extraction surgery (NOSES) is currently a research hotspot. Compared to traditional laparoscopic radical colorectal cancer resection, laparoscopic NOSES possesses advantages in reducing postoperative pain, incidence of infection at the incision site, and other related complications [1–3]. Moreover, it improves surgical esthetics and reduces gastrointestinal recovery time so patients may receive enteral nutrition earlier [4, 5]. However, various problems and technical bottlenecks in the development of NOSES of colorectal cancer exist [6, 7] including (1) the operation time of NOSES is longer; (2) the technical requirements of NOSES for the surgical team are relatively higher; (3) when extracting the specimen through the anus or vagina, squeezing the tumor, which may lead to tumor cell dissemination, is unavoidable; (4) to reconstruct the digestive tract, an opening on intestine is required but may easily cause pelvic and abdominal infections; and (5) a potential risk of vagina and anus strain injury is present when specimens are extracted through these structures.

The aforementioned ideas are built according to the current development of laparoscopic NOSES in colorectal cancer. No studies pertaining to robotic NOSES have been previously discussed. However, innumerable merits in robotic surgery have been reported including (1) filter physiological trembling; (2) magnification and provision of a three-dimensional view of the surgical field of view; and (3) accurately cutting, separating, and suturing even in narrow pelvic spaces [8–10]. These technical advantages have created satisfactory conditions in shortening the operation time and reducing the postoperative complication rate such as anastomotic fistula, abdominal infection, and abdominal hemorrhage [11]. To our knowledge, no trials in regard to robotic NOSES for colorectal cancer have been conducted. Hence, this randomized controlled trial is being performed to assess whether robotic NOSES is non-inferior to traditional robotic-assisted surgery for patients with colorectal cancer in terms of primary and secondary outcomes.

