## Methods/design

### Objectives

By comparing traditional robotic-assisted surgery, we aim to evaluate the perioperative safety and efficacy of robotic natural orifice specimen extraction surgery.

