### Sample size

A previously published study observed that the complication rate of robotic-assisted colorectal surgery is 17% [12]. According to the retrospective analysis in the medical record system at our institution, the complication rate of traditional robotic-assisted surgery is around 15%. As for the non-inferiority margin, no published studies can be referenced to our knowledge. After a close discussion with the investigators involved in this trial, the margin was set to 10%. We assume that this trial has 80% power (1-β) to detect the complication rate difference between the experimental and control group and a one-sided significance level of 0.025(α = 0.025). Accordingly, 402 participants in total are needed (201 per group). Considering that the overall dropout rate is 20%, we calculated that 503 participants should be enrolled in the study. Finally, 550 participants were recruited in this trial. The sample size was calculated using PASS 11 (version 11.0.7).

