### Statistical analysis

Non-inferiority analysis of primary outcomes will be performed in the per-protocol population using the chi-squared test with a one-sided significance level of 0.025, in which the power to detect the surgical complication rate difference is 0.8. The per-protocol population refers to cases that completed the corresponding treatment in each group. All analyses will be performed using SPSS 22.0 (IBM, USA). Both primary and secondary outcomes will be analyzed in accordance with the per-protocol principle. Subgroup analyses will be performed on these variables: gender (between male and female), approach (between vagina and rectum), and cT stage. Unadjusted *p* values will be reported but the number of declared subgroups analyses will be specified in all publications. Multiplicative interaction analysis will be applied, as appropriate.

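### The aim claims non-inferiority on primary and secondary outcomes, but only the 30-day complication rate has a margin, a sample size and a planned non-inferiority analysis

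*Protocol article*

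**What the plan says.** The abstract's Background and the Introduction give the same aim. The Introduction has: "assess whether robotic NOSES is non-inferior to traditional robotic-assisted surgery for patients with colorectal cancer in terms of primary and secondary outcomes". The Objectives section is more general ("we aim to evaluate the perioperative safety and efficacy of robotic natural orifice specimen extraction surgery") and mentions neither non-inferiority nor superiority.

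The Sample size section holds the only margin: "After a close discussion with the investigators involved in this trial, the margin was set to 10" per cent. It sits in a calculation for the complication rate, where "the complication rate of traditional robotic-assisted surgery is around 15" per cent. The Statistical analysis section plans a non-inferiority analysis of the primary outcome at one-sided 0.025. For everything else it says: "Both primary and secondary outcomes will be analyzed in accordance with the per-protocol principle". It defines the per-protocol set as patients who completed their allocated treatment, and the Intervention section removes non-adherent cases from it.

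The abstract's Discussion adds that "robotic NOSES is expected to exhibit superiority to traditional robotic-assisted surgery in terms of both primary and secondary outcomes".

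**The concern.** Non-inferiority is defined by a margin: the confidence interval must exclude a loss of a stated size. Without one, the word has no testable meaning for that outcome. The likely substitute is a non-significant difference, which does not show that harm has been excluded.

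This matters because of where the safety questions lie. Among the known problems of NOSES, the Introduction lists longer operating time, possible spread of tumour cells during extraction, and pelvic or abdominal infection from opening the bowel. Operation time, ascitic cytology and ascitic bacterial culture measure these directly, and all three are secondary outcomes without a margin. A report that followed the stated aim could call robotic NOSES non-inferior on tumour-cell spread from data unable to show it.

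The per-protocol rule adds a second difficulty. Dropping non-adherent or incomplete cases after randomisation can make the groups unlike each other, so a difference found in that set, on any outcome, may partly reflect who was removed.

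**Working it through.** **1. Reproduce the plan's sample size.** Inputs from the Sample size section: control rate 15%, margin 10 points, one-sided alpha 0.025, power 80%. Allocation is 1:1 (Randomization and blinding). The experimental rate is not stated; I assume it equals the control rate.

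n per group = (z₀.₉₇₅ + z₀.₈₀)² × 2p(1 − p) / margin²
= (1.960 + 0.842)² × 2 × 0.15 × 0.85 / 0.10²
= 7.849 × 0.255 / 0.01 = 200.2, so 201 per group and 402 in total.

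With 20% dropout, 402 / 0.80 = 502.5, so 503. Both figures match the plan exactly. The calculation uses one endpoint and one margin; no secondary outcome enters it.

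**2. Count the outcomes covered by the aim.** The Secondary outcomes section names:
- 7 stress or immune markers (C-reactive protein, IL-6, IL-10, cortisol, CD3, CD4, CD8);
- 2 ascitic-fluid rates;
- 8 general measures (pain, first flatus, leaving bed, first liquid diet, hospital stay, operation time, blood loss, lymph nodes).

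7 + 2 + 8 = 17 variables. Number with a margin: 0. Number with a planned non-inferiority analysis: 0.

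**3. What a non-significant result would show.** The article gives no rate of positive ascitic cytology, so the rates here are assumptions, shown as a range. Take a true doubling, 201 per group, two-sided 5%.

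Chance of non-significance ≈ 1 − Φ(d / SE − 1.960), with SE = √{[p₁(1 − p₁) + p₂(1 − p₂)] / 201}.

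| Assumed rates | SE | d / SE | Chance of non-significance |
|---|---|---|---|
| 2% vs 4% | 0.0170 | 1.18 | 78% |
| 3% vs 6% | 0.0206 | 1.46 | 69% |
| 5% vs 10% | 0.0262 | 1.91 | 52% |

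Across this range, a doubling would be missed more often than found.

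**4. The superiority expectation.** The trial was not sized for it. Take 15% against an assumed 10% complication rate, two-sided 5%:
- 201 per group: SE = √(0.2175 / 201) = 0.0329; 0.05 / 0.0329 = 1.52; power = Φ(1.52 − 1.96) = 33%.
- 275 per group (all 550 enrolled, none lost): SE = 0.0281; 0.05 / 0.0281 = 1.78; power = Φ(1.78 − 1.96) = 43%.

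**The case against.** The best defence is that this is loose wording in a condensed article. The Objectives section is neutral, the Statistical analysis section confines non-inferiority to the primary outcome, and nothing says a non-significant difference will be read as non-inferiority. The article's main Discussion concedes that further indicators, such as survival, are still needed. A fuller analysis plan may exist. All of this is fair, and it limits the point to a mismatch between aim and analysis. It does not remove the point: the broad aim is stated twice, and the analysis section contradicts it within the same document.

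Three stronger readings are tempting but not supported.

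- **That superiority is a trial objective.** It appears only as an expectation in the abstract's Discussion. The design is labelled non-inferiority and no superiority test is planned.
- **That the lack of a testing order for secondary outcomes is an error.** This is commonly left to an analysis plan, which is not shown. For the primary outcome, testing superiority after non-inferiority is a fixed sequence and needs no alpha adjustment.
- **That the plan carries a known, large chance of false positive findings.** Any such figure depends on how many tests are counted, on independence, and on every outcome supporting a formal claim. The article lists 17 variables, does not say that each marker is tested separately on each day, and does not say that each outcome will carry a claim. The outcomes are also plausibly correlated.

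**Conclusion.** The concern holds as a mismatch between aim and design. The stated aim covers 17 secondary variables for which the design has no margin, no sizing and no planned non-inferiority analysis. The trial can conclude non-inferiority on 30-day complications and on nothing else. The primary endpoint, margin, alpha and sample size are not put in doubt by this; 201, 402 and 503 all reproduce.

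The superiority expectation and the per-protocol-only analysis are supporting points. If a difference were claimed, it would come from a population selected after randomisation, in a trial with roughly 33% to 43% power for an assumed fall in complications from 15% to 10%. The article does not allow the size or direction of any per-protocol bias to be worked out.

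The mismatch itself rests on the text alone. The cytology and superiority figures rest on assumed rates and only illustrate the consequence.

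**What to change.** - In the abstract's Background and the Introduction, limit the non-inferiority aim to 30-day surgical complications.
- Report secondary outcomes as between-group differences with 95% confidence intervals in all randomised patients, with the per-protocol analysis as support.
- State that a non-significant difference on a secondary outcome is not evidence of non-inferiority.
- Either remove the superiority expectation from the abstract's Discussion, or state that superiority on the primary outcome is tested only once non-inferiority is met, in all randomised patients.

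The cost is changed wording in the aim and analysis sections, an added analysis in all randomised patients, and fewer formal claims on secondary outcomes. The sample size does not change.

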## Methods/design

### Objectives

By comparing traditional robotic-assisted surgery, we aim to evaluate the perioperative safety and efficacy of robotic natural orifice specimen extraction surgery.

### Trial design

This study is a prospective, open-label, randomized controlled, parallel-group, multicenter, and non-inferiority trial conducted in seven academic hospitals in China. The hospitals involved are shown in Table 1.

**Table 1 Tab1:** Collaborator hospitals, locations, principle investigator/collaborator and anticipated participants

Hospitals	Locations	Names	Role in this study	Anticipated participants
The First Affiliated Hospital of Nanchang University	China, Jiangxi	[name],	Principle investigator	130
		[name]	Steering committee	
		Division of data management	Data management team	
The Second Xiangya Hospital of Central South University	China, Hunan	[name]	Collaborator	70
Nanfang Hospital, Southern Medical University	China, Guangdong	[name]	Collaborator	70
First Affiliated Hospital of Gannan Medical College	China, Jiangxi	[name]	Collaborator	70
Zhongshan Hospital, Fudan University	China, Shanghai	[name]	Collaborator	70
Chinese PLA General Hospital (301 Hospital) China	China, Beijing	[name]	Collaborator	70
The Second Affiliated Hospital of Nanchang University	China, Jiangxi	[name]	Collaborator	70

### Inclusion criteria

The inclusion criteria are as follows:
Age ≥ 18 and ≤ 80 years;Performance status of 0 or 1 on ECOG (Eastern Cooperative Oncology Group) scale;Histological or cytological confirmation of colorectal adenocarcinoma;High rectal and sigmoid cancer with the lower margin of the tumor greater than 10 cm from the anal dentate line;T1-3N0M0 at preoperative evaluation according to the American Joint Committee on Cancer (AJCC) Cancer Staging Manual 8th Edition, transvaginal NOSES procedure with a specimen with a circumferential diameter of < 5 cm;Preoperative examination did not suggest distant metastasis, implantation, or invasion of adjacent organs;Cardiopulmonary liver and kidney function can tolerate surgery; andWritten informed consent for participation in the trial.

### Exclusion criteria

The exclusion criteria are as follows:
Not suitable for robot laparoscopic surgery;The tumor is too large to be pulled out through the anus or vagina;Simultaneous multiple primary cancers;Emergency surgery due to complication (bleeding, obstruction, or perforation) caused by primary cancer; andWomen with acute gynecological infections, vaginal deformities, unmarried and infertile women, and women who are married and plan to get pregnant.

### Withdrawal criteria

The withdrawal criteria are as follows:
Postoperative pathology confirmed the tumor is pT4 or N1–2;Intraoperative exploration or postoperative pathology confirmed distant metastasis;During the treatment period, the patients received other therapies other than this study regimen;Intraoperative exploration requires combined visceral resection;Postoperative pathology confirmed non-rectal adenocarcinoma; andAfter being enrolled in the study, the patients were required to be withdrawn from the study cohort for various reasons.

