### Postoperative management

Patients in both groups will receive the same care after surgery, and adjuvant therapy will be implemented in accordance to the NCCN guidelines for colon and rectal cancer.

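### The withdrawal criteria remove randomised, already operated patients from the cohort, conflict with the per-protocol definition, and leave unclear what the 20% dropout allowance covers

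*Protocol article*

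**What the plan says.** Patients enter on preoperative stage T1-3N0M0 (Inclusion criteria), are allocated once judged eligible, and then have the allocated operation (Recruitment and participants). The Withdrawal criteria apply afterwards. They cover:

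- upstaging: "Postoperative pathology confirmed the tumor is pT4 or N1–2";
- metastasis found at surgery or on pathology;
- a need for combined visceral resection found at surgery;
- during the treatment period, that "the patients received other therapies other than this study regimen";
- pathology showing non-rectal adenocarcinoma;
- after enrolment, that "the patients were required to be withdrawn from the study cohort for various reasons".

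The primary outcome is surgical complications at 30 days (Primary outcomes). Patients and surgeons are not blinded (Randomization and blinding). Primary and secondary outcomes are analysed per protocol, meaning cases that completed the corresponding treatment in their group, and no other analysis set is named (Statistical analysis). Non-adherent cases also leave the per-protocol analysis (Intervention). The Sample size section needs 402 evaluable patients, allows for loss ("Considering that the overall dropout rate is 20" per cent) to reach 503, and then sets 550. Under Postoperative management, "adjuvant therapy will be implemented in accordance to the NCCN guidelines for colon and rectal cancer".

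**The concern.** The intervention is a single operation. Withdrawal on a pathology report cannot stop that treatment; its only possible effect is on whether the patient's data are used. Yet the 30-day complication outcome can be observed whatever the report says.

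Three things are at stake. First, the analysed population is not determinate, because the withdrawal list and the per-protocol definition give different answers for the same patient. Second, grounds that arise during or after surgery, and one with no stated limit, are applied where the arm is known. If removal is related to both arm and complications, the comparison is no longer protected by randomisation, and no analysis of all randomised patients is planned as a check. Third, the plan does not say whether the 20% allowance covers these withdrawals, so the evaluable number cannot be judged.

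**Working it through.** **Who is analysed.** Take a patient with clinical T1-3N0M0 disease who has the allocated operation and is then found to be N1. Under the Withdrawal criteria this patient leaves the cohort. Under Statistical analysis the patient completed the corresponding treatment and is per protocol. Both cannot hold.

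**The plan's sample size.** Inputs from Sample size: complication rate 15% (the rate in the experimental arm is not stated; equality is assumed), margin 10 points, one-sided α 0.025, power 80%. Allocation is 1:1 (Randomization and blinding).

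n per arm = (1.96 + 0.8416)² × 2 × 0.15 × 0.85 / 0.10² = 7.849 × 0.255 / 0.01 = 200.1, rounded up to 201, so 402 in total. With 20% loss, 402 / 0.80 = 502.5, rounded up to 503. Both of the plan's figures reproduce.

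**Loss that 550 tolerates.** (550 − 402) / 550 = 148 / 550 = 26.9%.

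**Power by total loss.** Power = Φ(0.10 / √(0.255 / n) − 1.96), where n is the evaluable number per arm. The loss values are assumptions.

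| Total loss | Evaluable of 550 | n per arm | Power |
|---|---|---|---|
| 0% | 550 | 275 | 90.7% |
| 20% | 440 | 220 | 83.6% |
| 25% | 412.5 | 206.25 | 81.2% |
| 30% | 385 | 192.5 | 78.5% |
| 35% | 357.5 | 178.75 | 75.4% |
| 40% | 330 | 165 | 72.0% |

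Two assumed combinations bracket the break-even point. Stage withdrawal of 15% with 10% other loss gives 1 − 0.85 × 0.90 = 23.5% loss, 421 evaluable and 81.9% power. Stage withdrawal of 20% with 10% other loss gives 1 − 0.80 × 0.90 = 28% loss, 396 evaluable and 79.6% power.

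**How selective removal could act.** This is an illustration with assumed rates. Let the true rates be 15% (control) and 25% (NOSES), exactly at the margin, with 275 per arm. If 10% of complicated NOSES cases are withdrawn (0.10 × 0.25 × 275 ≈ 7 patients) and nobody else, the analysed NOSES rate is 0.225 / 0.975 = 23.1%. The chance of wrongly declaring non-inferiority then rises from 2.5% to 8.3%. With 20% of them withdrawn, the rate is 0.20 / 0.95 = 21.1% and the chance is 22.1%. Removal concentrated in the control arm would act the other way.

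**The case against.** Several points on the other side are sound.

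- **Stage and bias.** A reader might infer that the pathology criterion itself biases the comparison. True stage is fixed before randomisation and allocation is stratified by cT stage and hospital, so it should balance. A route through node yield is conceivable, since retrieved nodes are a secondary outcome, but nothing in the documents says yield differs by arm.
- **Other therapies.** One might read this item as removing patients treated for a complication. The text does not say so; it is limited to the treatment period, and both arms receive the same postoperative care. Adjuvant therapy can likewise be read as part of the regimen. What stands is that the treatment period and the regimen are undefined, so the two sections need reconciling.
- **Data loss.** It is not established that withdrawn patients leave the primary analysis. The per-protocol definition would keep many of them, and the consent form asks whether data may be used if a participant chooses to withdraw. That is why this is a conflict to resolve and not a proven loss.
- **The open-ended item.** It does not say who requires the withdrawal, so it does not show that site staff may remove anyone they choose. It also sets no limit. The final analyst is blinded to allocation, but that does not cover withdrawal decisions taken earlier at the sites.
- **Per-protocol analysis.** It has a proper place in a non-inferiority trial, because keeping patients who had a different operation can dilute a true difference. This argues for having both sets, not for per-protocol alone.

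**Conclusion.** The point holds as a conflict over the analysed population, combined with avoidable exclusions after randomisation. The pT4 and N1–2 criterion mainly costs power and narrows the population. The open-ended item, and the other grounds arising during or after surgery in an open-label trial, can bias the result, possibly towards non-inferiority. Neither the direction nor the size can be known from the documents.

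A reader might conclude that the trial will exceed its dropout allowance and be underpowered. The documents do not support that: they give no upstaging rate, and raising enrolment from 503 to 550 lifts the tolerable loss to 26.9%. Power stays above 80% at 25% loss and falls below it at 28%. These figures assume a 15% rate in both arms and the normal approximation that reproduces the plan's 201 per arm. The 90.7% figure assumes no loss at all, so it is an upper limit.

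**What to change.** 1. For the 30-day primary endpoint, analyse all randomised patients who had surgery, in their allocated arm, whatever the pathology or intraoperative findings.
2. Report the per-protocol set alongside, using the completed-treatment definition already given, and require the two to reach consistent conclusions.
3. Turn the withdrawal items into recorded flags for sensitivity analyses.
4. Delete the open-ended last item. Limit removal of data to withdrawn consent for data use, which the consent form already asks about.
5. State what the 20% covers.
6. Reconcile two pairs of sections: the item on other therapies with the adjuvant therapy under Postoperative management, and the item on non-rectal adenocarcinoma with the Inclusion criteria, which admit sigmoid cancer. Read literally, that item would withdraw every sigmoid case.

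The cost is an amendment to the Withdrawal criteria, Sample size and Statistical analysis sections, plus 30-day outcomes for operated patients already withdrawn. The main set will include some pT4, node-positive or combined-resection patients, which may slightly dilute a difference; the per-protocol analysis addresses this. Requiring both sets to agree means that power is at most that of the less powerful of the two analyses.

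### A withdrawal criterion worded for rectal tumours contradicts the inclusion of sigmoid cancer and, read literally, withdraws every eligible sigmoid patient after surgery

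*Protocol article*

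**What the plan says.** The Inclusion criteria define the population by histology and by site. The histology item is "Histological or cytological confirmation of colorectal adenocarcinoma". The site item is "High rectal and sigmoid cancer with the lower margin of the tumor greater than 10 cm from the anal dentate line". Sigmoid tumours are therefore enrolled on purpose.

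The Withdrawal criteria list findings at operation or on pathology that take a patient out of the study. Among them is "Postoperative pathology confirmed non-rectal adenocarcinoma". Its neighbours concern pT4 or node-positive disease, distant metastasis and combined visceral resection.

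The abstract, introduction and discussion all put the question for patients with colorectal cancer. The Statistical analysis section analyses primary and secondary outcomes per protocol, and defines that population as cases that completed the treatment of their group.

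**The concern.** The withdrawal item can be parsed in two ways: an adenocarcinoma that is not rectal, or any finding other than rectal adenocarcinoma. A sigmoid adenocarcinoma meets both. A patient can thus satisfy every inclusion criterion, be randomised, have the allocated operation, and then meet a withdrawal criterion because of a tumour site that the trial deliberately admits.

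If sites followed the text, an intended part of the population would be withdrawn after randomisation. If those patients also left the analysis, the result would apply to upper rectal cancer only and would rest on fewer patients than planned.

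**Working it through.** **The texts side by side**

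| Item | Inclusion criteria | Withdrawal criteria |
|---|---|---|
| Histology | colorectal adenocarcinoma | rectal adenocarcinoma implied as the only acceptable finding |
| Site | high rectum or sigmoid | rectum only, on the literal wording |
| When assessed | before randomisation | on postoperative pathology |

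No other section limits the withdrawal item to non-colorectal tumours or to histology other than adenocarcinoma. The contradiction is complete on the wording and needs no arithmetic.

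**The plan's own sample size**

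Inputs from the Sample size section: "the complication rate of traditional robotic-assisted surgery is around 15" per cent; "the margin was set to 10" per cent; one-sided alpha 0.025; power 80%; overall dropout 20%; enrolment 550. The same 15% rate is taken in both arms, which reproduces the stated figure.

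- Per group: n = (1.960 + 0.842)² × 2 × 0.15 × 0.85 / 0.10² = 7.849 × 0.255 / 0.01 ≈ 200.1, rounded up to 201, or 402 in total. This matches.
- With dropout: 402 / 0.80 = 502.5, rounded up to 503. This matches.
- With 550 enrolled and 20% lost: 550 × 0.80 = 440 evaluable. Power = Φ(0.10 / √(0.255/220) − 1.960) = Φ(0.977) = 83.6%.

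The sample size itself is not in question.

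**What literal application could cost**

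Let s be the sigmoid share. The document does not give it, so the values below are assumptions. The calculation also assumes that withdrawn patients leave the analysis. The number left is N = 550 × (1 − s), multiplied by 0.80 if the full dropout is added. Power = Φ(0.10 / √(0.255/(N/2)) − 1.960).

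| s | N, no other loss | Power | N, 20% dropout added | Power |
|---|---|---|---|---|
| 10% | 495 | 87.6% | 396 | 79.6% |
| 30% | 385 | 78.5% | 308 | 69.1% |
| 50% | 275 | 64.1% | 220 | 54.7% |
| 70% | 165 | 43.6% | 132 | 36.3% |

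Worked for s = 30%:

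- No other loss: 0.10 / √(0.255/192.5) = 2.748; 2.748 − 1.960 = 0.788; Φ = 78.5%.
- Dropout added: 0.10 / √(0.255/154) = 2.457; 2.457 − 1.960 = 0.497; Φ = 69.1%.

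The 402 evaluable patients are kept up to s = 1 − 402/550 = 26.9% with no other loss, and up to s = 1 − 402/440 = 8.6% with the full dropout added. The two columns are bounds: the Sample size section calls the 20% an overall rate, so it may already cover withdrawals.

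**The case against.** The strongest reply is that nobody meant this. Site is settled at eligibility, before randomisation. The withdrawal item depends on what pathology newly reveals, and its neighbours are findings of that kind. Its natural purpose is to catch a tumour that turns out not to be the eligible adenocarcinoma. Against the rest of the article, a slip for non-colorectal is much the likeliest explanation. This stands, and it lowers the weight of the point. It does not remove it, because sites act on the text of a withdrawal rule and this text is wrong for part of the intended population.

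A reader might go further and infer three things that the document does not support.

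- **That the trial will lose power.** A sigmoid patient who had the allocated operation meets the stated definition of the per-protocol population, and the Statistical analysis section does not say that withdrawn patients are excluded. The consent form also asks about use of data from participants who choose to withdraw. On the other side, the last withdrawal item speaks of removal from the study cohort. The document leaves this open, and it gives no sigmoid share.
- **That the rule would be applied unevenly across the seven hospitals.** This is possible with ambiguous wording, but nothing in the document shows it.
- **That the comparison would be biased between arms.** Site is fixed before allocation, so exclusion on site alone would mainly cost precision and generalisability. The document shows no mechanism that differs by arm.

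Whether a per-protocol analysis alone is adequate is a separate question. This wording does not settle it.

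**Conclusion.** The contradiction between the Inclusion criteria and the Withdrawal criteria is real. Read literally, the rule withdraws all eligible sigmoid patients after randomisation and surgery and conflicts with the stated colorectal population. It is an inconsistency of wording in an operative rule, probably unintended, and not a chosen design feature. It should be corrected, but it is not evidence that the trial is underpowered: if sigmoid patients stay in, the figures of 402 and 503 stand, and 550 enrolled gives 83.6% power after 20% dropout.

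The losses in the table arise only if three conditions hold together: sites apply the literal wording, withdrawn patients leave the per-protocol set, and the sigmoid share is large enough. The lower column also adds the whole 20% dropout. At an assumed 30% share without other loss, power falls only slightly below the target; the larger falls need a higher share or the added dropout.

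**What to change.** Reconcile the two sections so that the withdrawal criterion matches the eligible histology, for example: *postoperative pathology does not confirm colorectal adenocarcinoma*. Add that a sigmoid site alone is not a ground for withdrawal. Send the corrected text to all seven hospitals through the amendment route described under Trial status.

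The cost is a change of a few words and a note to investigators. The sample size need not change.
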